### **3.7 Expected duration of the trial**

The end of the trial will be defined as 28 days post-delivery or discharge from hospital (whichever sooner) of the last recruited participant and infant. To achieve our projected numbers, we will involve at least three centres, each receiving referrals from satellite units, and will recruit over a 36 month period. Each site has a busy preterm birth surveillance clinic, with approximately 500 women screened each year. We anticipate that 30% of these (120/year) will develop a short cervix (< 25mm, based on our current EQUIPP database >20000 women at high risk of sPTB), and 50% (60) will be willing to be randomised in an RCT. Therefore over 36 months with recruitment from 3 centres, we would potentially be able to randomise 540 women with short cervixes.

### **3.8 Linkage of data**

At the time of recruitment a unique study number will be allocated to the patient. Data will be recorded on a password protected KCL computer in order that recruits can be contacted and delivery outcomes recorded. The anonymised research record will not contain any patient identifiable data. All records will be anonymised at time of data entry in accordance with the Data Protection Act 1998.

A bespoke internet based data management system has been designed and built by MedSciNet and maintained by them. Varying levels of access are available from simple user to global administrator, each level requiring individual log-in and password. Minimal identifiers will be used on the main study database (initials, date of birth and unique study number). Contact details to ensure data completeness will be stored on a separate database linked only to study ID. Data will be entered directly into the Preterm Birth Studies database, and data quality will be assured by regular data monitoring. Women will be followed up until postnatal discharge. Paper copies of consent forms will be stored numerically (by study ID) and kept in a secure location in accordance to the Data Protection act 1998.

## **4 Biological samples**

### **4.1 Sample collection and processing**

#### **4.1.1 Cervicovaginal fluid**

Participants will be asked to lie on a couch, having removed their underwear, with a sheet over their waist to maintain dignity. They will be aware that a speculum will be used in the collection of their routine clinical fFN swab. A chaperone will be present.

The speculum will be inserted with water or a pea-sized amount of KY jelly as lubricant (because of the quantitative nature of the test, lubrication should be minimal to avoid any contamination of the swab but allow easy insertion of the speculum).

Approximately 4 swabs will be taken for a single speculum. For a high vaginal sample (for biomarkers and microbiology samples), the swab will be inserted into the posterior fornix of the vagina and rotated 360°. It should be in the posterior fornix for 10 seconds, and then removed. For an endocervical sample, the swab or cytobrush will be taken from the cervical os and rotated 360 degrees for 10 seconds. The whole process will take up to 30 seconds. A qfFN sample will be taken from the posterior fornix, rotated for 10 seconds, and processed according to manufacturer's instructions using the Rapid 10Q qfFN analyser.

#### **4.1.2 Saliva sample**

Participants will be asked to rinse their mouth thoroughly with water 10 minutes prior to producing the sample. The start time will be noted, and a sample of at least 5 ml of saliva will be collected into a 30 ml universal specimen container over approximately 10 minutes. The sample will be kept on ice between each salivation.

#### **4.1.3 Blood samples**

A phlebotomist, midwife or doctor will take 15 ml of blood via venepuncture into one EDTA and SST tube.

[figure not shown]

## 4.2 Storage

Samples and data will be stored for 25 years. Biological samples will be preserved and stored in accordance with the Human Tissue Act (2004). Samples will be stored in -80°C freezers in a secure freezer corridor. These are regularly maintained via company maintenance contracts. All the -80°C freezers are alarmed, and this is transmitted to via text message to the mobile phones of designated research staff. Freezer temperatures are recorded online and can be monitored remotely via the internet. All samples will be barcoded. Barcodes will link to study ID number. Information will be limited to members of the research team. Samples must be assigned a unique code as soon as possible after acquisition. The code will be unique to the group and the coding system designed in such a way that a code cannot be used more than once. A link between the participant consent form and the uniquely assigned code will be maintained to facilitate identification of stored material from participants who subsequently revoke consent. The participant id will be added to the consent form, which is then stored securely.

## 4.3 Analysis

Biological samples of saliva, blood and cervico-vaginal secretions will be stored for future analysis of candidate and other biomarkers implicated in preterm birth. A variety of molecular and proteomic approaches will be used to determine biomarker status (e.g. inflammatory markers can be measured using a range of immunoassays, Western blot, mass spectrometry and novel aptamer arrays). Swabs taken for microbiome studies will be analysed using a combination of microarray techniques and PCR techniques. A range of genomic approaches will be used for genetic analyses (DNA, RNA).

## 5 Sample size, power and statistical analysis

Our previous experience (captured by a robust database of outcome data from >2000 women attending our prematurity clinic) indicates that approximately 50% of women with short cervixes (<25 mm) treated with cerclage deliver early <37 weeks. From existing published evidence, we have good reason to believe that cerclage, vaginal progesterone and silicone pessary are all of approximately equal efficacy and reduce the rate of prematurity in women from 75% (untreated) to around 50% [6,8,9,15]. We therefore determine to confirm this by a 3-arm equivalence study. Equivalence is defined as agreement to within 20% (e.g. 40% to 60%). Following Jones *et al* (1996), we allow for differences in both directions in calculating the power. Complete data on 170 women per arm (510 in all) will give us 90% power to detect difference clinically important differences of 20% or more in either direction. To allow for dropouts, we aim to recruit 540 women in total.

Analysis will be according to intention to treat. The main outcome is delivery before 37 weeks'. Results will be presented as both odds ratios and risk differences, leading to number needed to treat (NNT) if appropriate, according to CONSORT guidelines. Given that high risk women with a history of invasive cervical surgery, and those with incidental findings of a short cervix may have a different pathophysiology to those women with a history of preterm birth, sub-group analysis will be performed according to risk factor. As we are powering for equivalence in the maternal outcome, it is not anticipated that the neonatal outcomes will be different however we will collect data on composite neonatal end point (not specifically powered for equivalence).

For biomarker analysis, results will be analysed at each time point in a cross sectional analysis, and on a case-control basis. We will express the overall usefulness of each marker for prediction of the primary outcome as a ROC area (Receiver Operating Characteristic), with 95% confidence interval and p-value. We will describe the performance of the most useful markers in terms of sensitivity, specificity and related measures for selected cut-points. We will use logistic regression in order to identify possible useful combinations of markers; where possible, we will use the repeated measurements to describe the change in test performance with gestation.

[figure not shown]

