#### 3.4.2 Vaginal progesterone

No significant adverse events have been reported with 200 mg vaginal progesterone. Vaginal progesterone once daily will be prescribed at the time of recruitment. Patients will be informed to insert vaginal progesterone every day until 34 weeks' gestation (or delivery, whichever is soonest). The patient will usually be followed up with two to four weekly transvaginal ultrasound scans (or more frequently if clinically indicated) according to local protocols. If the cervix shortens and membranes are visible, prior to 24 weeks' gestation, a rescue cerclage will be inserted, according to local protocols. Vaginal progesterone will be stored as per manufacturers instructions and dispensed by the hospital pharmacy. Licensed indications are for adjunctive use with oestrogen in post-menopausal women with an intact uterus (HRT). Progesterone will not be used within its licensed indications for this study. Any preparation of vaginal progesterone (200 mg) currently used in clinical practice for the prevention of preterm birth, will be allowed for use in the trial (eg Cyclogest, Uterogestan) according to individual site clinical protocols.

Contraindications are:

- known allergy or hypersensitivity to progesterone.
- severe hepatic dysfunction,
- undiagnosed vaginal bleeding,
- mammary or genital tract carcinoma,
- thrombophlebitis,
- thromboembolic disorders, • cerebral haemorrhage,
- porphyria.

[figure not shown]

If unexplained, sudden or gradual, partial or complete loss of vision, proptosis or diplopia, papilloedema, retinal vascular lesions or migraine occurs during therapy, the drug should be discontinued and appropriate diagnostic and therapeutic measures instituted. Vaginal progesterone 200mg should be used cautiously in patients with conditions that might be aggravated by fluid retention (e.g. hypertension, cardiac disease, renal disease, epilepsy, migraine, asthma); in patients with a history of depression, diabetes, mild to moderate hepatic dysfunction, migraine or photosensitivity and in breast-feeding mothers. Any adverse events experienced should be recorded as per the AE/ SAE section 8 of this protocol.

Indications for stopping treatment are:

- Elective (preterm) delivery
- Fetal membrane rupture
- Symptomatic placenta praevia
- Sudden or gradual, partial or complete loss of vision,
- Proptosis or diplopia
- Papilloedema
- Other patient reaction or sensitivity to progesterone
- Patient request

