### **3.4.3 Cervical pessary**

The product must be stored at room temperature. The appropriately sized (see appendix 1) pessary will be inserted within 7 days of recruitment by the attending clinician, who will be trained in the procedure. They will be given detailed written instructions about its subsequent management. It will be removed by a trained clinician at 37 weeks' gestation (or in the event of established labour). The patient will be usually be followed up with two to 4 weekly transvaginal ultrasound scans (or more frequent if clinically indicated) according to local protocols. If the cervix shortens and membranes become visible prior to 24 weeks' gestation, a rescue cerclage will be inserted, according to local protocols

Indications for stopping treatment include:

- Pessary dislodges or falls out twice or more
- Patient request

There might be some increase in vaginal discharge, however there is no evidence to suggest increased risk of infection or other complications.

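### The protocol names intention to treat as the only basis for its equivalence claim, and that basis is not conservative when women cross over or when both arms stop treatment at similar rates

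*Protocol*

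**What the plan says.** Protocol Section 5 expects the three treatments to have about the same efficacy and states: "We therefore determine to confirm this by a 3-arm equivalence study". Equivalence means agreement to within 20 points, with 40% to 60% given as the example. The analysis basis is one sentence: "Analysis will be according to intention to treat". The protocol names no other analysis population for the primary endpoint.

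Elsewhere it describes several ways of departing from the allocated treatment:
- **Rescue cerclage.** In the progesterone arm (Section 3.4.2), if membranes become visible before 24 weeks, "a rescue cerclage will be inserted, according to local protocols". Section 3.4.3 says the same for the pessary arm.
- **Stopping.** The listed reasons for stopping the pessary include "Pessary dislodges or falls out twice or more" and the woman's request. Section 3.4.2 lists reasons for stopping progesterone. The withdrawal section lets women stop drug or pessary at any time.
- **Other crossover.** Section 2.5.3 excepts the other study products from permitted concomitant medication, so crossover other than rescue is a deviation.

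Compliance and changes to the intervention are recorded (Sections 3.4.2 and 3.6, Schedule of Visits), and rescue cerclage is a secondary endpoint (Section 2.4.2). Section 5 uses none of these to support the equivalence conclusion.

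**The concern.** In a superiority trial, mixing the treatments works against the sponsor's claim, so intention to treat is cautious. In an equivalence trial the damaging error is to call different treatments equivalent, and mixing makes that error more likely.

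The consequence is practical. The synopsis and Section 2.2 ask whether the treatments are equally efficacious, and Section 1.3 says that a finding of equal efficacy would allow surgery to be avoided. A false finding would therefore feed straight into treatment choice. The increase from 510 to 540 women covers dropout only and makes no allowance for crossover.

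**Working it through.** **Inputs from Section 5.** Margin ±0.20; 170 evaluable women per arm; stated power 90%; 75% preterm if untreated; about 50% expected in every arm. The cerclage figure comes from the sponsor's own database: "approximately 50% of women with short cervixes (<25 mm) treated with cerclage deliver early <37 weeks". No significance level is given, only that "we allow for differences in both directions in calculating the power". I assume a two-sided 95% confidence interval that must lie wholly within ±20 points, for one pair of arms.

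**The plan's own figure.** With 50% in both arms:
- SE = √(2 × 0.25/170) = 0.0542
- Power = 2Φ(0.20/0.0542 − 1.96) − 1 = 2Φ(1.728) − 1 = 91.6%
- Required n = 2 × 0.25 × (1.960 + 1.645)²/0.20² = 162.4, so 163 per arm

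The stated 90% with 170 per arm is reproduced to within 2 points, which supports the assumed rule.

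**Crossover.** Let the true rates be 70% and 50%, exactly at the margin. A share c of the worse arm takes the better treatment and gets its rate. Then:
- p₁ = 0.70 − 0.20c, p₂ = 0.50, d = 0.20(1 − c)
- SE = √[p₁(1 − p₁)/170 + 0.25/170]
- P(declare equivalence) = Φ((0.20 − d)/SE − 1.96); the opposite limit contributes nothing material here

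| c (assumed) | d | SE | P(declare equivalence) |
|---|---|---|---|
| 0% | 0.20 | 0.0520 | 2.5% |
| 5% | 0.19 | 0.0522 | 3.8% |
| 10% | 0.18 | 0.0525 | 5.7% |
| 20% | 0.16 | 0.0528 | 11.5% |
| 30% | 0.14 | 0.0532 | 20.3% |

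If 5%, 10% or 20% of each arm switch to the other, d = 0.20(1 − 2c) and the chance is 5.7%, 11.6% or 32.9%.

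**Stopping without switching.** Let women who stop revert to the untreated 75%.
- *Both arms, same share c:* p₁ = 0.70 + 0.05c and p₂ = 0.50 + 0.25c, so again d = 0.20(1 − c). At 10%, 20% and 30% the chance is 5.8%, 11.8% and 21.4%.
- *Worse arm only, 20%:* p₁ = 0.71, d = 0.21, SE = 0.0518. The chance is Φ(−0.01/0.0518 − 1.96) = Φ(−2.153) = 1.6%, below the nominal 2.5%.

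**Why rescued women should not be excluded from a per-protocol set.** Suppose (assumed) that 10% of the 70% arm are rescued and all of them deliver preterm. Removing them leaves (0.70 − 0.10)/0.90 = 66.7% among 153 women, against 50% among 170. The difference falls to 16.7 points, SE = 0.0541, and false equivalence in that set is Φ(0.0333/0.0541 − 1.96) = about 9%. The exclusion creates the distortion the set is meant to guard against.

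**Power of a per-protocol set.** With equal true rates of 50% and 180 randomised per arm, 2Φ(0.20/SE − 1.96) − 1 gives:
- about 90% at 162 per arm (10% excluded)
- about 87% at 150 (17% excluded)
- about 85% at 144 (20% excluded)

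**The case against.** The strongest reply is that Section 5 does not say *only* intention to treat. Per-protocol sets and adherence definitions are often left to a statistical analysis plan, which is not available here and may supply them. That stands in part: the lack of a detailed definition is no fault. But the protocol does state the basis for its primary conclusion, and by itself that basis guards an equivalence claim poorly.

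A reader might also infer more than the documents support:
- **That every departure pulls the arms together, so the error grows in proportion to non-adherence.** It does not. Stopping in the worse arm alone widens the difference. Placement of the cerclage or pessary within 7 days of recruitment (Sections 3.4.1 and 3.4.3) is protocol care, not non-adherence.
- **That rescue cerclage makes intention to treat invalid.** Rescue is written into the progesterone and pessary arms. For the question of which strategy to start with, intention to treat is the right analysis. The crossover table does not describe rescue either: it gives switchers a 50% rate, which Section 5 reports for cerclage in women with a short cervix, whereas rescue follows visible membranes, a state that excludes women at entry (Section 2.5.2).
- **That error rates of 10% to 20% are to be expected.** The protocol gives no switching or stopping rates, and at 5% one-way switching the rise is small.

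**Conclusion.** The point holds in a limited form. The protocol declares equivalence as its aim and names intention to treat as the only analysis basis. That basis is not conservative against crossover to another arm's treatment, or against similar rates of stopping in both arms. At the margin, one-way switching of 5% to 30% raises false equivalence from 2.5% to between 3.8% and 20.3%.

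These figures assume a 95% interval rule, a true difference exactly at the margin, 170 women per arm, and switchers who gain the full benefit of the better arm. The mechanism is certain; its size in this trial cannot be known from the protocol. It bears on the primary conclusion, and the data needed for a safeguard are already collected. The documents do not support the broader inference that all non-adherence favours equivalence, or that rescue cerclage invalidates the primary analysis.

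**What to change.** Amend Section 5, and carry the change into the statistical analysis plan:

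1. Keep intention to treat as the primary analysis, and state that it estimates the effect of each strategy including protocol-specified rescue cerclage.
2. Conclude equivalence for a pair of arms only if the 95% confidence interval for the risk difference lies within ±20 points in the intention-to-treat set and also in a pre-specified per-protocol set.
3. Define the per-protocol set as: allocated treatment started within the protocol window, adherence at a pre-set level, and no non-protocol use of another arm's treatment. Sections 2.3 and 3.4 describe the timing of pessary insertion and of cerclage differently, so those passages must be reconciled before the window is used.
4. Keep women who receive protocol-specified rescue cerclage in the per-protocol set, in their allocated arm.
5. Treat any analysis that counts rescue as failure as supportive only. Rescue is specified in two arms, so such an analysis penalises those two by construction.

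The cost is wording plus one further analysis of data already recorded. The second set is smaller, with the power shown above, and requiring both sets to pass cannot raise power. Per-protocol selection can introduce bias, which is why it supplements intention to treat and does not replace it. The adherence definition must be fixed before the data are analysed.

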### 1.4 Rationale for pre-intervention predictive biomarker testing in parallel

Whilst sPTB culminates in a common pathway of myometrial activation, cervical dilation and rupture of membranes, it is initiated by a number of different factors, which hinders accurate identification of at risk women and application of a 'one size fits all' preventative intervention. It is anticipated that the multiple pathways and pathologies preceding cervical shortening and sPTB, and thus a woman's response to various preventative interventions, may be differentiated by the expression of different biomarkers. We predict that the observed intervention effects may be enhanced by selection of sub-groups of women according to their biomarker expression i.e. that the underlying pathophysiology may determine the success of one intervention over the other. 'Pre-intervention' samples of blood, saliva and CVF will be taken from all women when randomised, and two weekly thereafter until 24 weeks' (or delivery). Biomarkers measured will include fFN, natural antimicrobial peptides and other inflammation related markers and salivary progesterone, whilst creating a biobank of samples for future analysis of other potential candidate biomarkers. We will also analyse blood biomarkers and DNA extracted from whole blood for genetic differences (e.g. SNP polymorphisms) in women destined to deliver prematurely during pregnancy compared to those who deliver at term. Bacterial and viral DNA/RNA extracted from vaginal swabs to determine the relationship between candidate biomarkers the vaginal microbiome and response to intervention. ≥

[figure not shown]

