### **2.3 Trial Design**

An open label, multi-centre three armed randomised controlled trial. Women who develop a short cervix will be randomised to one of 3 treatments: cervical cerclage (procedure to take place within 7 days of diagnosis, removed at 37 weeks'), cervical pessary (inserted at diagnosis and removed at 37 weeks'), vaginal progesterone (200 mg once daily per vagina until 34 weeks' gestation from time of randomisation). At an appropriate time-point between time of randomisation and time of intervention, women will provide a saliva sample, CVF sample and blood sample (for biomarker analysis, optional, if facilities allow). These will be repeated every approximately every two weeks according to routine clinic visits thereafter until 28 weeks' gestation.

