#### **2.4.2 Secondary endpoints**

- i) Adverse perinatal outcome, defined as a composite outcome of death (antepartum/intrapartum stillbirths plus neonatal deaths prior to discharge from neonatal services) or one (or more) of intraventricular hemorrhage,

[figure not shown]

periventricular leukomalacia, hypoxic ischemic encephalopathy, necrotizing enterocolitis, bronchopulmonary dysplasia and sepsis.

- ii) Delivery <30 & 34 completed weeks' gestation.
- iii) Gestation at delivery.
- iv) Time between intervention and delivery.
- v) Requirement for Rescue Cerclage (bulging fetal membranes).
- vi) Other maternal and fetal outcomes: clinical course, therapies administered, maternal and fetal morbidity and mortality data until discharge or 28 days post-natal (whichever soonest).
- vii) Participant and clinician's perceptions of treatment: questionnaires with a selection of participants at 0-2 weeks post procedure. Questionnaires at one year are planned if funding is obtained.
- viii) Health costs at 28 days post-natal.
- ix) Biochemical end-points (on available samples): cervical swabs will be taken to determine the presence of cervicovaginal infection and concentrations of biomarkers of preterm birth, infection and inflammation. Saliva samples will be collected for salivary hormone levels, and blood samples taken for inflammatory markers and genetic analysis. Results will be correlated with maternal and fetal outcomes.

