### **3.3 Study visit 1: Randomisation and intervention (14+0-23+6 weeks' gestation)**

At time of recruitment women will be randomly assigned (1:1:1) to cerclage, progesterone or pessary. Randomisation will be carried out online via the Medscinet web portal ([www.medscinet.net](http://www.medscinet.net)). Users will be assigned a personal identifier number. Due

[figure not shown]

to the nature of the interventions, the study is not blinded to the clinician or patient. Recruiters and trial coordinators will not have access to the randomisation sequence. Women will be informed at time of recruitment to which arm they have been randomised. A 'minimisation' procedure, using a computer-based algorithm, will be used to avoid chance imbalances in important stratification variables. Stratification variables will be a) gestation, b) BMI <30 or >30 kg/m^2 c) risk factor (previous premature delivery <24 weeks & previous cervical surgery). Women will not know what treatment they will be allocated prior to recruitment. Medscinet will write the randomisation program and hold the allocation code. Contact information will be obtained from the patient. Demographic measures will be entered into the central trial database. Following randomisation, the obstetrician will then arrange for the intervention to be performed as the randomisation indicates. There is no 'emergency code break' procedure as the trial is an open label RCT.

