### **3.5 Pre- and Post intervention biomarker measurement**

At a convenient time between randomisation and intervention, the following procedures will take place in order to obtain biomarker levels (if study site facilities allow and the participant has consented to them):

[figure not shown]

- a) One sterile speculum examination and approximately 4 cervico-vaginal swabs (high vaginal and/or endocervical). The speculum examination will last approximately 20-30 seconds (normally 15 seconds if only 1 swab is taken as per routine clinical care after 18 weeks'). qfFN will be performed from 18 weeks' gestation.
- b) A saliva sample (5 ml) will be obtained.
- c) Two blood samples will be taken (2 x 15 ml/1 tablespoon), one for genetic analysis; one for biomarker analysis.

CVF sampling will be repeated, if facilities allow, at each subsequent routine clinic visit until 28 weeks' gestation. Sample collection is not mandatory for trial participation. Some women may only want to provide samples at a single visit or only provide one or more of the samples listed.

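### Section 5 sets no arm restriction for salivary progesterone as a predictor after treatment starts, when one third of women are taking progesterone, and the timing rules do not secure a pre-dose first sample

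*Protocol*

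**What the plan says.** **Marker.** Section 1.4 lists salivary progesterone among the biomarkers to be measured. Section 2.4.2 confirms it as part of a secondary endpoint: "Saliva samples will be collected for salivary hormone levels". Section 1.2.3 gives the reason: low values, or a blunted rise at 24 to 34 weeks, in women who deliver early.

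**Analysis.** Section 5: "For biomarker analysis, results will be analysed at each time point in a cross sectional analysis, and on a case-control basis". Each marker's usefulness for predicting the primary outcome is a ROC area with a 95% confidence interval and p-value. Where possible, repeat measurements show how performance changes with gestation. Neither arm nor progesterone exposure is mentioned.

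**Exposure.** Section 3.3: "At time of recruitment women will be randomly assigned (1:1:1) to cerclage, progesterone or pessary". In Section 2.3 the progesterone arm receives "200 mg once daily per vagina until 34 weeks' gestation from time of randomisation". Section 3.4.2: "Vaginal progesterone once daily will be prescribed at the time of recruitment".

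**First sample.** Section 3.5: "At a convenient time between randomisation and intervention, the following procedures will take place". Section 2.3 places it in the same interval. The Schedule of Visits lists sampling under screening and randomisation, and none under the day 0 intervention.

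**Repeat samples.** Section 2.3, of saliva, cervicovaginal fluid (CVF) and blood: "These will be repeated every approximately every two weeks according to routine clinic visits thereafter until 28 weeks' gestation". Section 1.4 repeats the same three every two weeks, but only to 24 weeks or delivery. Section 3.5 repeats CVF alone, to 28 weeks.

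**The concern.** Salivary progesterone is the one named marker that is also a study drug. In samples taken on treatment, a woman in the progesterone arm may show her own level plus an effect of the dose. If the arms are analysed together, that added variation obscures any link between the woman's own level and preterm birth.

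The gestations at issue are the ones the rationale relies on. The group's own evidence in Section 1.2.3 concerns 24 to 34 weeks. Randomisation closes at 23+6 weeks, so every trial sample from 24 weeks onward follows allocation.

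Two things are at stake. A marker that works in untreated women could look weaker than it is, and a decline in performance after baseline could be read as an effect of gestation when part of it is dosing. Separately, the exploratory objective in Section 2.2 rests on pre-intervention status. A first saliva sample taken after a dose would not provide that, and no later analysis could repair it.

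**Working it through.** **The plan's own figures.** The protocol states no ROC area for salivary progesterone and no size for any rise under vaginal treatment, so there is no figure to reproduce on this point. The one calculated figure in Section 5, 90% power with 170 women per arm, concerns the primary outcome. It reproduces closely if a 95% two-sided interval is assumed: 2Φ(0.20/√(2 × 0.5 × 0.5/170) − 1.96) − 1 = 0.916. Nothing below depends on it.

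**Step 1: inputs.**
- Share of women on progesterone: 1/3, from 1:1:1 allocation (Section 3.3).
- Preterm rates: equal in all arms, as Section 5 expects (about 50%).
- True ROC area without exposure: 0.70 or 0.80 (assumed).
- Rise in salivary progesterone on treatment: s standard deviations, unrelated to outcome (assumed).
- Marker: normal with equal variance in women who do and do not deliver preterm.

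**Step 2: formula.** Draw one woman who delivers preterm and one who does not. With equal rates, each is in the progesterone arm with probability 1/3.
- Both exposed or both unexposed: 1/9 + 4/9 = 5/9. The shift cancels.
- Only one of them exposed: 2/9 for each direction.

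With d = √2 × Φ⁻¹(true area):

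pooled area = 5/9 × Φ(d/√2) + 2/9 × [Φ((d + s)/√2) + Φ((d − s)/√2)]

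**Step 3: numbers.** For a true area of 0.70, d = 0.742. The first term is 5/9 × 0.70 = 0.389.
- s = 1: 0.389 + 2/9 × (0.891 + 0.428) = 0.682
- s = 2: 0.389 + 2/9 × (0.974 + 0.187) = 0.647
- s = 4: 0.389 + 2/9 × (1.000 + 0.011) = 0.613
- very large s: 0.389 + 2/9 = 0.611

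| Assumed rise (SD) | True area 0.70 | True area 0.80 |
|---|---|---|
| 0 | 0.700 | 0.800 |
| 0.5 | 0.695 | 0.794 |
| 1 | 0.682 | 0.776 |
| 2 | 0.647 | 0.727 |
| 3 | 0.622 | 0.689 |
| 4 | 0.613 | 0.672 |
| limit | 0.611 | 0.667 |

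A simulation with 20,000 cases and 20,000 controls per arm agrees: 0.681, 0.647 and 0.614 for rises of 1, 2 and 4 SD from a true 0.70.

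**Step 4: unequal preterm rates.** Suppose the progesterone arm has a rate of 40% or 60% against 50% elsewhere. A marker with no predictive value then gets a pooled area of about 0.54 or 0.46 at s = 3, scoring low values as predicting preterm birth. Pooling can therefore create a signal as well as weaken one.

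**Step 5: timing of the first sample.** Sections 2.3 and 3.5 define the window as after randomisation and before treatment. For cerclage it can last up to 7 days (Section 3.4.1). For progesterone, Section 2.3 starts treatment at randomisation and Section 3.4.2 prescribes it at recruitment, so read literally the window has no length. No passage requires the saliva sample to precede the first dose.

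**Step 6: repeat sampling.** Sections 1.4 (three sample types, to 24 weeks), 2.3 (three types, to 28 weeks) and 3.5 (CVF only, to 28 weeks) cannot all be followed. Under 1.4, sampling stops where the group's own 24 to 34 week evidence begins. Under 3.5, there is no on-treatment saliva. Under 2.3, the problem arises in full.

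**The case against.** The strongest reply is that Section 5 never says the arms are pooled. It fixes the time structure and a ROC area per marker, but not which women contribute. The objective concerns response to each intervention, which invites analysis by arm, and a statistical analysis plan that is not shown may provide it. This stands: pooling is a reading of the text, and the losses above are conditional on it. The point survives because Section 5 does fix the time points and the use of repeats, and names no exception for the marker that is also a treatment. Section 1.2.2 does report that elafin was unaltered by treatment; nothing similar is said for salivary progesterone.

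A reader might infer that the protocol allows the first sample to be taken after progesterone has started. It does not say so. Sections 2.3 and 3.5 and the Schedule of Visits all intend a pre-treatment sample. Prescribing and pharmacy dispensing (Section 3.4.2) are not a first dose, and Section 2.5.2 excludes women already on progesterone to prevent preterm birth beyond 14 weeks. What remains is a conflict of wording and the lack of a rule tying the sample to the first dose.

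It is also fair that sampling is optional and depends on facilities (Section 3.5), and that repeats are used only where possible (Section 5). Because women know their arm and may decline individual samples, uptake could differ by arm, but nothing in the protocol shows that it would.

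**Conclusion.** The point holds as a flaw in an exploratory analysis and as two contradictions in the sampling rules. If Section 5 is applied to post-baseline saliva from all arms together, the ROC area for salivary progesterone is diluted: from 0.70 to about 0.68, 0.65 or 0.61 for rises of 1, 2 or 4 SD, and never below 0.611. This rests on equal preterm rates, a normal marker, a rise unrelated to outcome, and a size of rise that the protocol does not give. At 1 SD the loss is only about 0.02.

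It would be too strong to say that the marker measures the drug. That could apply only to samples taken on treatment in one of three arms; samples taken before dosing and the cerclage and pessary arms are unaffected. Nor do the documents show that the marker would be wrongly dismissed, or that any fall in performance would be wholly artefact. The supportable statement is that a change from baseline could partly reflect dosing. The primary endpoint, the sample size and the comparison of treatments are untouched.

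**What to change.** 1. **Sections 2.3 and 3.5.** State that the first saliva, CVF and blood samples are taken at the screening/randomisation visit, where the Schedule of Visits already places them, before any study treatment and preferably before allocation is disclosed. Reconcile this with the statement in Section 2.3 on when progesterone begins. The change concerns the time of sampling, not of treatment.
2. **Section 5.** Analyse post-baseline salivary progesterone by arm, or in the cerclage and pessary arms only. Examine other post-baseline markers by arm before any pooling.
3. **Sections 1.4, 2.3 and 3.5.** Reconcile which samples are repeated and until what gestation.

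The cost is protocol wording and a by-arm analysis, with no new samples. If the analysis is restricted to the two unexposed arms, it loses about one third of the women for this one exploratory marker. The timing of the first sample is the urgent part, since it cannot be corrected at analysis.
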